2. **Experimental design:** 18-month worksite randomized controlled trial, in which worksites are randomized to receive the multiple intervention wellness programs or the control program. Control participants will participate in outcomes assessments only for the first 6 months, after which they will enroll in the intervention of their choosing. Both arms (HPI and the iDiet) will receive direct training from the coaches who deliver these commercial programs at their respective worksite and/or via a concurrent online session, or at an alternative commutable location that is offsite in the case of the HPI program. A total of 400 participants in the worksites allocated to the intervention, with approximately 20 participants in the HPI arm and 30 in the iDiet arm per worksite is planned to ensure even balance in each of the study arms. If more than 20 individuals are interested in and eligible for the HPI arm or more than 30 are interested in and eligible for the diet arm, participants will be enrolled into the study on a first-come, first-serve basis, including a small upward or downward adjustment in the total number of employees enrolled per site to ensure that the overall targeted number of participants is achieved. All participating individuals, from both the intervention wellness and control programs, can opt-in to either the HPI or the iDiet weight loss program. However, if they choose to participate in the weight loss intervention they will then be randomized into one of two groups: iDiet with food provided or iDiet with a gift card,. The study flow and primary intervention groups are described below:

**
[figure not shown]
**

*^1^The number of controls reflects study design in which sign up for the intervention and distribution of the intervention sites happens before baseline to ensure equivocal disposition*.

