- Group 1: Human Performance Institute (HPI) training workshop: Is comprised of a comprehensive individual development training program that focuses on the concept of energy management. The training includes sections on a conscious evaluation of one’s goals in life, tips to manage and improve personal energy to achieve goals, as well as sessions on nutrition and exercise. The primary aim of this program is to help individuals develop attitudes, habits, and behaviors that increase their levels of daily energy, life satisfaction, and overall functioning. The course is delivered over 2.5 days in a group format with 25 – 32 participants per group by 3 coaches, each of whom specializes in one of the areas described above. Online support modules and supporting educational materials will be available to participants for the remaining 12 month period.
- Group 2: Intensive iDiet group behavioral weight loss program delivered in-person at the worksite or by videoconference and with support of the program’s web platform; This intervention will be delivered by trained nutritionists and will consist of 1-hour support and education meetings of approximately 15 participants/group with weekly messages via the iDiet message board for individual support. The 1-hour meetings will be weekly for 24 weeks (the “active weight loss” period) and then reduced to approximately once a month for the remainder of the 18-month trial. Additionally, following the weekly classes online support will also be provided for the remainder of the study (“structured maintenance” period) with additional booster classes provided on an as-needed basis. The intervention involves a diet behavioral program with particular emphasis on hunger reduction and craving control for both weight loss and prevention of weight regain.

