The increase in vitality score in the intervention worksites compared to controls is expected to be 9 points at both time points compared to the control. Since randomization is at the worksite level, the total variance includes both the within worksite and between worksite variance. Based on a within worksite standard deviation of 15 and 20 people per worksite and a between worksite standard deviation of at most 3.4, 12 worksites with a 2:1 worksite allocation in favor of treatment are needed to have 80% power to detect an expected increase in vitality score of 9 points.

For the participants electing to participate in the behavioral weight loss program, randomization to either with provided Yevo foods or a gift card such that one half of the participants are in one group and the other half will be assigned to the remaining arm.. Assuming worksite is a fixed variable, 8 worksites with 30 subjects each (240 total subjects) is at least 80% powered to detect a 2.4% difference in weight loss with provided food compared to gift cards assuming no diet by food interaction. If there is a significant food by diet interaction, the study will have an 80% power to detect an interaction that is a 4.5% difference in weight change with provided food for iDiet and 3% improvement in diet.

Data analyses will be performed using the latest version of SAS for Windows, currently 9.4 (Cary, NC: SAS Institute Inc.). All testing will be two-sided and results will be judged statistically significant if the observed significance level (P value) is <0.05. Data will be examined graphically and numerically for outliers and other aberrations that might lead to misleading results. Data may be transformed prior to formal analysis if necessary to fit the assumptions for the statistical model to be employed. Both studies (HPI intervention and the iDiet intervention) will be analyzed according to Intention-To-Treat principles to best reflect what happens when individuals start one of the interventions. If necessary, missing data will be estimated using multiple imputations using the MI Procedure of SAS for Windows.

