For the HPI intervention in whom those randomized to intervention will be compared primarily with subjects at control sites who elected the HPI intervention prior to workplace randomization, a mixed linear model with worksite nested within the randomization to HPI intervention or control as a random factor will be use to assess the effect of the intervention on change in vitality scale score. Baseline vitality score, weight, ethnicity and gender will be included as covariates.

The diet intervention will compare those receiving the iDiet with a primary outcome of percent change in weight at 6 and 18 months. To assess the effect of diet and food delivery method, a multi-factor model with diet, food and worksite as independent variables will be used, controlling for baseline weight, gender and ethnicity. Interactions between diet and worksite, food and worksite and food and diet will be assessed and included in the final model if significant. Change in weight for the HPI intervention andchange in vitality score for those in the diet intervention will be included as secondary outcomes.

Secondary analyses will include a comparison of the 3 intervention arms (with and without provided food for the iDiet) as well as the combined effect of intervention on change in anthropometric measures including body fat, and also lipids, blood glucose levels and blood pressure using the same models described above adjusting for the appropriate baseline values. Additionally, regression models will be used to assess the effect of different adherence metrics, activity levels, appetite regulation (hunger and food cravings) and measures of wellbeing on outcome measurements both within and between intervention groups for each arm of the study. In addition, predictors of changes in cardiometabolic parameters will be examined. Prior to enrollment of subjects, a formal data analysis plan will be prepared and submitted as part of clinical trial registration.

1. **Worksite Characteristics**

A convenient sample of worksites in the Greater Boston area, consisting of worksites which have previously expressed interest, and respond to the recruitment letters will be invited to participate in the Worksite Wellness Study. The first twelve eligible worksites with a higher employee interest in worksite wellness will then be invited to enroll in the study.

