4. Economic risk: It is possible that the participant may have to pay for a doctor’s visit if an in-person visit is required to obtain the physician clearance form. A small stipend is provided to cover such incidental expenses. No additional payment will be provided.

No compensation will be provided for missed work time for study activities however this will be planned with employee and management support to minimize/avoid missed work time and will be counted as credit rather than as time off.

For the diet arm of the study, class will only be for one hour during lunch or at another convenient time identified by the participants and facilitated by mutual agreement between the iDiet group leader and management. However, if the participants prefer a concurrent online session then intervention delivery will be provided using the online groups with flexibility for some in person groups. No compensation will be provided for missed work time for these classes. However, time required for study activities will be planned with employee and management support to minimize/avoid the impact of missed work time and will be counted as credit rather than as time off.

For the HPI program, a one-time initial workshop involving two and a half days will be required. No compensation will be provided, however time required for study activities will be planned with employee and management support to minimize/avoid the impact of missed work time and will be counted as credit rather than as time off. Please note that both weekend and weekday times will be offered for sign-up and if a participant absolutely cannot take a weekday off, they will have the option to choose weekend times, such as a Friday afternoon through the weekend.

1. Benefit of participation: The direct benefit is the opportunity of receiving a commercial diet or wellness program free of charge. This study has the potential for improved wellness for the participants in the areas of energy, health and weight related wellness. Furthermore, it is anticipated that findings from these studies will help to advance nutrition research.
2. **Specific methods and techniques used throughout the study**

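### The primary HPI model and its 80% power allow only for worksite clustering, although at the stated group sizes workshops would probably cross worksites

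*Protocol*

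**What the plan says.** All places are in the protocol; no SAP is at hand.

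- **Group size.** The Group 1 (HPI) description says the course is delivered "in a group format with 25 – 32 participants per group by 3 coaches".
- **Site quota.** Experimental design plans "approximately 20 participants in the HPI arm and 30 in the iDiet arm per worksite", with a small adjustment up or down allowed. The sample size section uses 20 per worksite, with 8 intervention and 4 control worksites.
- **Place and time.** Experimental design names delivery at the respective worksite, online, or "at an alternative commutable location that is offsite in the case of the HPI program". The Economic risk item says that "both weekend and weekday times will be offered for sign-up". The Transportation item, by contrast, says that all support takes place in the workplace.
- **Power.** The vitality difference "is expected to be 9 points at both time points compared to the control". With a within-worksite SD of 15 and a between-worksite SD of at most 3.4, "12 worksites with a 2:1 worksite allocation in favor of treatment are needed to have 80% power". No other source of variance is counted.
- **Primary model.** It is "a mixed linear model with worksite nested within the randomization to HPI intervention or control as a random factor", with baseline covariates. No workshop or coach term appears.
- **Controls.** They have outcome assessments only for the first 6 months.

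**The concern.** People who spend 2.5 days in one group with the same three coaches may end up more alike than people taught in different groups. If a workshop draws from several worksites, its shared effect links those worksites, whereas the model takes them as independent given the arm. Controls attend no workshop before the 6-month comparison, so the extra correlation sits in one arm only and randomising worksites does not cancel it.

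Two things are at stake, and they depend on how people reach the sessions:

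- **Each site scattered over many sessions.** The workshop effect is nearly common to all intervention sites. It hardly shows as between-site variance, so the standard error is too small.
- **Whole sites pooled into workshops.** Much of the effect does show as between-site variance. The test stays roughly valid but loses power.

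**Working it through.** **Inputs from the protocol.** Difference 9; within-worksite SD 15 (variance 225); between-worksite SD 3.4 (variance 11.56, stated as a maximum); 20 per worksite; 8 and 4 worksites. The test follows the rule "All testing will be two-sided and results will be judged statistically significant if the observed significance level (P value) is <0.05".

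**Assumptions, because the protocol gives no figure.** Workshop ICC ρ is the share of the 225 that lies between workshops, taken as 0.01 to 0.10. The number of workshops G is 5 or 6.

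**Step 1: number of workshops.** 8 × 20 = 160 people. 160/32 = 5 and 160/25 = 6.4, so 5 or 6 workshops serve 8 worksites.

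**Step 2: the plan's own figure.** Variance of a worksite mean = 11.56 + 225/20 = 22.81. SE = √(22.81 × (1/8 + 1/4)) = √8.554 = 2.92. A two-sided noncentral t test with 12 − 2 = 10 df gives 79.2% power, so the stated 80% is reproduced.

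**Step 3: add workshops in the intervention arm.**

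Var = 11.56/8 + 11.56/4 + ρ × 225/G + (1 − ρ) × 225/160 + 225/80

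For ρ = 0.05 and G = 6: 1.445 + 2.890 + 1.875 + 1.336 + 2.813 = 10.36, so SE = 3.22 and power = 71% on 10 df.

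| Workshop ICC | SE (G = 5; 6) | Power, 10 df |
|---|---|---|
| 0.01 | 3.00; 2.99 | 77–78% |
| 0.02 | 3.07; 3.05 | 75–76% |
| 0.05 | 3.28; 3.22 | 70–71% |
| 0.10 | 3.59; 3.49 | 62–64% |

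With only G + 2 df the four rows become 73–75%, 71–74%, 66–69% and 58–62%. Adding the workshop variance on top of the 225, instead of taking it from within it, changes little: 69–71% at 0.05 and 60–63% at 0.10 on 10 df.

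**Step 4: a smaller worksite SD.** At SD 1.7 (variance 2.89) and no workshop effect, the variance is (2.89 + 11.25) × 0.375 = 5.30 and power is 94%. At ρ = 0.05 and G = 6, it is 2.89 × 0.375 + 1.875 + 1.336 + 2.813 = 7.11, SE = 2.67 and power is 86% (84% with G = 5). Power falls but stays above 80%.

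**Step 5: the worksite-only test by layout.** This is a simulation of the t test on worksite means (equivalent to the balanced mixed model), with 5 or 6 workshops, worksite SD 3.4 and at least 40,000 trials per scenario.

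| Workshop ICC | Every site spread over all sessions: false positives | Whole sites pooled: false positives |
|---|---|---|
| 0.02 | about 6% | 5–6% |
| 0.05 | 7–8% | 5–6% |
| 0.10 | 9–10.5% | 5–6% |

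At ICC 0.05 the worksite-only test has about 78% power in the spread layout, partly because its standard error is too small, and about 71% in the pooled layout. At worksite SD 1.7 and ICC 0.05 the spread layout gives about 8–9% false positives, so a small worksite SD protects power but not the error rate.

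**The case against.** **Mixing is not stated.** A reader might infer that workshops must combine worksites. The documents do not support that as fact. Delivery at the respective worksite is the first route named, the Transportation item places all support in the workplace, and the worksite eligibility list has each company help run the workshop on assigned dates. The 25 to 32 is not called a minimum, and the 20 is approximate. One undersized workshop per worksite would make workshop and worksite coincide, and the worksite random effect would absorb the workshop effect, though in one arm only. This stands as a limit on certainty. Mixing is still the natural reading. Even 700 enrolled gives about 58 per site and, at 20:30, about 23 for HPI, which is still below 25. Reaching 25 at all 8 sites means 200 people instead of 160. Weekday and weekend sign-up makes single-site groups smaller still.

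**A fixed 70% is not in the documents.** A reader might infer that true power is about 70%. That needs a workshop ICC of 0.05, which is an SD of √11.25 = 3.35, about as large as the whole worksite SD and additional to it at its ceiling. If the 3.4 already stands for the workshop SD, power is 75–78% on 10 df. This objection stands.

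**The two harms do not occur together at full size.** The largest error inflation belongs to complete spreading and the largest power loss of the planned test to pooling. Partial splitting falls between. This also stands.

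**Detail belongs in the SAP.** The protocol promises a formal analysis plan, and a df method can wait for it. The random-effect structure and the variance sources behind the 80% are, however, already fixed in the protocol.

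**Conclusion.** The point holds in conditional form. At the stated sizes HPI workshops would probably cross worksites, and neither the primary model nor the power calculation allows for it. The 80% is correct on its own inputs and silently assumes no workshop clustering.

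The size depends on an assumed workshop ICC, the worksite SD and the layout. With the worksite SD at its maximum, power runs from 77–78% (ICC 0.01) to 62–64% (ICC 0.10); with a smaller SD it can exceed 80%. The false-positive rate runs from near 5% when sites are pooled to 9–10.5% at ICC 0.10 when every site is fully spread. The documents support neither a single corrected power nor the statement that mixing is certain. The change is worth making because it concerns a primary test and workshop membership is hard to reconstruct afterwards.

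**What to change.** 1. Reconcile Experimental design, the Group 1 description, the Economic risk item and the Transportation item on HPI group size and place of delivery, and state whether a workshop may combine worksites.
2. Record for each HPI participant the workshop signed up for and the workshop attended.
3. If workshops cross worksites, add workshop to the primary HPI model as a random effect in the intervention arm only (zero variance in controls), crossed with worksite, with a small-sample df method.
4. In the sample size section, say that the 80% assumes no workshop clustering and give power over a stated range of workshop ICCs, without replacing it by a single 70%.

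**Cost.** Two data fields, one variance component and a less favourable power statement; no extra participants. With 5 or 6 workshops the component will be imprecisely estimated and may come out as zero, and the confidence interval may be slightly wider.

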Anthropometry: The research coordinators will take duplicate fasting measurements of weight in program participants to ±0.1 kg at baseline, 6, 12, and 18 months in all subjects using the Tanita TBF300A, self-calibrating scale with 200kg capacity. Participants will be asked to wear light clothing and no footwear. In addition, height will be measured in duplicate to ±0.1 cm at baseline using a portable stadiometer (Seca 214). Fasted waist and hip circumference will be measured in duplicate to ±0.3 cm at baseline, 6, 12, and 18 months in all subjects according to our standard procedures (Seca 201). Fasted blood pressure will be measured to the nearest 1 mmHg at baseline, 6, 12, and 18 months in all subjects using a validated automated monitor (3 measurements, 5 minutes apart after 5 minutes of quiet sitting, using the OMRON HEM-705CP Digital Blood Pressure Monitor). Measurements that are out of range (systolic BP >160 mmHg, diastolic BP >100 mmHg) will be flagged in data given to participants, who will be recommended to follow up with their physician (please note: as stated earlier physician clearance will be required prior to enrollment for all participants).

Anthropometric measurements will be completed at the worksite by study staff using paper data collection forms and will then be entered into the online, password protected database, using their numerical ID. This form has identifiers because the use of electronic de-identified data forms is not feasible due to the large number of participants moving through the measurement stations which could potentially cause errors in measurement recording if the study ID was the only identifier. These forms will be transported from the study site in a locked briefcase and will be kept in a locked file cabinet at the USDA Human Nutrition Research Center on Aging, as detailed in the confidentiality section below.

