**Table 2: Overview of Questionnaires at Each Time point (in weeks):**

| **Questionnaires** | **Intervention Worksites – iDiet, and HPI Groups*** | **Control Worksites – Future iDiet, and HPI Groups*** |
| --- | --- | --- |
| **Demographics & Brief Medical History** | **0** | **0** |
| **Rand Quality of Life (SF-36)** | **0, 3, 6, 12, 18** | **0, 3, 6** |
| **IPAQ Physical Activity Questionnaire – Short form** | **0, 6, 12, 18** | **0, 6** |
| **Cravings Questionnaire** | **0, 6, 12, 18** | **0, 6** |
| **Three Factor Eating Questionnaire – R51** | **0, 6, 12, 18** | **0, 6** |
| **Food Preferences Questionnaire** | **0, 6, 12, 18** | **0, 6** |
| **MOS Sleep Questionnaire** | **0, 6, 12, 18** | **0, 6** |
| **Work Productivity and Impairment Scale (WPAI)** | **0, 6, 12, 18** | **0, 6** |
| **Ryff Purpose in Life Scale** | **0, 3, 6, 12, 18** | **0, 3, 6** |
| **Morningness Eveningness Questionnaire** | **0** | **0** |
| **Center for Epidemiologic Studies Depression Scale**  **(CES-D)** | **0, 6, 12, 18** | **0, 6** |
| **Profile of Mood States (POMs)** | **0, 6, 12, 18** | **0, 6** |
| **Cognitive Tests (computer based)** | **0, 6, 12, 18** | **0, 6, 12, 18** |

1. **Assessment of Participant Safety and Development of a Data and Safety Monitoring Plan (DSMP)**

A Data and Safety Monitoring Plan will be implemented to ensure the safety of the participants, as well as the validity and the integrity of the data. [name] with the help of the study physician and research coordinators will monitor all aspects of safety. A safety monitoring log will be developed and participants will be asked to record signs, symptoms and both serious and non-serious adverse events. Research assistants will be instructed to report any adverse events that occur during research activities to the PI as soon as possible. Both serious and non-serious events will be documented. An event will be considered serious if it results in death, is life-threatening, requires inpatient hospitalization, or results in a persistent or significant disability/incapacity, or might require medical or surgical intervention to prevent one of these outcomes. Non-serious events are defined as conditions that may be unpleasant to the participant, such as sore muscles, but do not require termination of participation. Any participant who experiences an adverse event has the option to continue participation in the study, if she so chooses and if it is safe and appropriate.

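### The stated primary models give no role to the interim weights and the 3-month SF-36, and nothing commits the conditional imputation to using them, so the 18-month food contrast is exposed to lost power and to bias in either direction

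*Protocol*

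**What the plan says.** All references are to the protocol.

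- **Weight model** (Sample size and statistical analyses). The diet comparison has a "primary outcome of percent change in weight at 6 and 18 months", analysed by a multi-factor model with diet, food and worksite, adjusted for baseline weight, gender and ethnicity. No visit effect, subject effect or within-person covariance is named.
- **Vitality model** (same section). A mixed linear model for change in the vitality score, with worksite nested in randomised condition as the random factor. It has no repeated-measures term either.
- **Missing data** (same section). Analysis is by intention to treat, and "If necessary, missing data will be estimated using multiple imputations using the MI Procedure". No trigger and no list of imputation variables is given. A formal analysis plan is promised before enrolment.
- **Data scheduled.** At intervention sites Table 1 lists weight at 0, 3, 6, 9, 12, 15 and 18. The Table 2 row "Rand Quality of Life (SF-36" lists 0, 3, 6, 12 and 18 there, and 0, 3 and 6 at control sites. Both tables are headed in weeks, but the numbers match the month schedule elsewhere and are read as months here.
- **Conflicting text.** Study Procedures (Anthropometry) has weight taken "at baseline, 6, 12, and 18 months in all subjects", without 3, 9 and 15.
- **Primary weight time points.** These are 6, 12 and 18 months where the sample-size section defines the outcome, 6 and 18 months where it describes the model, and 18 months under Outcomes.
- **Power** (Sample size and statistical analyses). For the contrast of Yevo foods against gift cards, the text claims that "8 worksites with 30 subjects each (240 total subjects) is at least 80% powered to detect a 2.4% difference in weight loss".

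**The concern.** Over 18 months of weight-loss follow-up, some participants will be lost, and loss may depend on how their weight has gone. The protocol itself makes this plausible: it withdraws people who join another weight-loss programme, assesses participants at the workplace, and accepts sites with employee turnover of about 15% (no time unit given). Someone who leaves after month 9 has weights at 3, 6 and 9 months that predict the missing 18-month value.

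A model of one change score at one visit uses none of that information unless it is brought in through imputation. The protocol neither fixes that imputation will happen nor says that interim values will be in it. At stake are the power of the 18-month food contrast, for which no dropout allowance is visible, and its validity if dropout depends on earlier weight change.

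**Working it through.** **1. Inputs.** From the documents: two-sided 0.05; 240 iDiet participants split 1:1, so 120 per arm; difference 2.4 percentage points; power 80%. Not in the documents, so assumed: SD of percent weight change (back-solved below), dropout d (15% and 30% shown) and the correlation ρ between an earlier weight change and the 18-month change (0.6 to 0.9).

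**2. The plan's own figures.**

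Food contrast: SD = 2.4 / [(1.960 + 0.842) × √(2/120)] = 6.64. With a t distribution on 231 df it is 6.61. The stated power therefore corresponds to an SD of about 6.6 with all 240 analysed. This agrees by construction and is not an independent confirmation.

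Vitality: SE = √[(3.4² + 15²/20) × (1/8 + 1/4)] = √(22.81 × 0.375) = 2.925. For 9 points, a noncentral t with 10 df gives 79.2%, which reproduces the stated 80%.

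**3. Food contrast if dropouts contribute nothing.** Power = Φ(2.4 / [6.64 × √(2/n)] − 1.960), with n = 120(1 − d).

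- d = 15%: n = 102, power 73.3%.
- d = 30%: n = 84, power 65.0%.

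Imputation from arm and baseline covariates alone would do little better, since it adds no post-baseline information on those who left.

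**4. Food contrast if earlier weights are used.** With one earlier weight observed on everyone, the effective number per arm is about 120(1 − d)/(1 − dρ²).

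| Dropout | Dropouts omitted | ρ = 0.6 | ρ = 0.9 |
|---|---|---|---|
| 15% | 73.3% | n = 107.8, 75.7% | n = 116.1, 78.7% |
| 30% | 65.0% | n = 94.2, 69.9% | n = 111.0, 76.9% |

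The gain is about 2 to 5 points at 15% dropout, 5 to 12 points at 30%, and zero with no dropout. It applies equally to a repeated-measures model and to imputation that includes the earlier weights.

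**5. Bias.** Simulation with 4,000 trials per pattern, 120 per arm, true difference −2.40, and 30–33% lost after month 6. The 3-month correlation is 0.9, so the 6-to-18-month correlation is 0.9⁴ = 0.66. Where dropout depends on weight, the log-odds slope is 0.8 per SD of the 6-month change, doubled in the food arm in the third row.

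| Dropout pattern | Complete cases | Using 6-month weight |
|---|---|---|
| Unrelated to weight | −2.40 | −2.41 |
| Poor losers leave, equally in both arms | −2.21 | −2.36 |
| Same, more strongly in the food arm | −2.87 | −2.42 |
| Only in the gift-card arm | −1.34 | −2.41 |

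The complete-case estimate can be unchanged, too small or too large. The estimate using the 6-month weight stays close to the truth in all four patterns.

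**6. Vitality.** Between-site variance is 3.4² = 11.56 of the 22.81 variance of a site mean, about half, and a 3-month score cannot reduce it. At 15% dropout (17 per site) power is 75.8% on complete cases, against 76.6% to 77.9% using the 3-month score with an assumed correlation of 0.5 to 0.8. The gain is 1 to 2 points.

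**The case against.** The strongest reply is that the protocol nowhere prescribes a completers-only analysis. It states intention to treat, provides for multiple imputation, and retains data collected before withdrawal. Imputation that includes the interim weights rests on the same missing-at-random assumption as a repeated-measures model and recovers about the same information. A baseline-adjusted change score at a named visit with imputation is a standard choice, and the imputation variables may properly sit in an analysis plan that is not shown.

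Most of this stands, and it limits the point. A reader might infer that the plan discards dropouts' data; it does not say so. The comparison above is therefore with what the text allows, not with what it orders. What remains is that the protocol does state its primary models, those models have no place for the interim visits, and imputation depends on an undefined judgement of need. The retention clause gives participant-flow reporting as its reason, not analysis.

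Two other tempting readings fail. The 12-month weight is not ignored: one definition of the primary outcome includes it, and the fault there is inconsistency. Nor must the food contrast shrink: the direction depends on who leaves which arm.

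**Conclusion.** The point holds in a limited form. As written, the primary models give no role to the 3-, 9- and 15-month weights or the 3-month SF-36, and nothing binds the imputation to use them. If dropouts are omitted, or imputed without interim values, power for the food contrast would be about 73% at 15% dropout and 65% at 30%, against roughly 76–79% and 70–77% with earlier weights. When dropout depends on earlier weight change, the estimate may be biased in either direction.

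These sizes are illustrative. The SD of about 6.6 is inferred from the stated power, and dropout and correlation are assumed because the documents give neither. Imputation that includes interim weights would largely remove the problem. For vitality the expected gain is small. This should be changed, but it does not invalidate the design.

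**What to change.** 1. Make the primary weight analysis a likelihood-based repeated-measures mixed model on percent change, with arm by visit, baseline weight, worksite, gender and ethnicity and a within-person covariance. Use every scheduled post-baseline weight, and read the 6- and 18-month contrasts from it.
2. Replace the conditional imputation wording with a fixed rule: the model above as primary, and multiple imputation that includes the interim values as a sensitivity analysis.
3. Treat vitality the same way with the 3- and 6-month SF-36, keeping the worksite random effect.
4. Reconcile Study Procedures (Anthropometry) with Table 1 on the 3-, 9- and 15-month weights, and state one set of primary weight time points in the outcome definition, the model description and Outcomes.

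**Cost.** Slightly more modelling work and changes of wording. If Table 1 governs, the data are already scheduled. If the Study Procedures text reflects what sites would do, the 3-, 9- and 15-month weights have to be collected as Table 1 lists them, and that is a cost in data collection.
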